### Sample size calculation

We have previously estimated that 23% of our HD population have IDH [38]. To estimate the sample size, we conservatively assumed that only one IDH episode would occur per run (although it is likely that more than one episode will occur per run, increasing the study power). With this approach, and using a 2 × 2 crossover design, we estimated that a sample size of 30 participants would provide a power of 90% to demonstrate a 30% reduction in the rate of IDH under the biofeedback treatment vs. the control treatment, with a two-sided alpha of 0.05. We will enroll 34 participants to guard against dropout, which can be as high as 30% [41]. These estimates are based on simulation studies assuming only one IDH episode per run and two Poisson processes with average rates of IDH equal to 7 (control) and 5 (intervention) episodes over 24 runs. We used R (R Foundation for Statistical Computing, Vienna, Austria) [49] for simulations, and the package clusterPower in R.

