### Statistical analysis

We will use mixed-effects Poisson regression to test the null hypothesis that the ratio of the rate of IDH episodes (main model exposure) during the intervention phase over the rate of IDH episodes during the control phase will range between 0.7 and 1.3 (i.e., the alternative two-sided hypothesis is that the incidence rate ratio will be 0.7 or lower). We will study the effect of the intervention as a fixed effect and account for the correlation in the data due to the subject using random effects. The multi-level model will have errors due to within-subject variation and due to between-cluster variation (between subject variance). In the event that the study generates over-dispersed data, we will use a negative binomial regression with the approach as described above. We will also explore whether participants with larger drops in systolic blood pressure (>30 mmHg) benefit from the planned intervention. They will be analyzed as a subgroup.

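### The stated error terms of the primary Poisson model leave out extra-Poisson change between a participant's two phases, and whether the negative-binomial fallback repairs this depends on an unstated unit of analysis

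*Protocol article*

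**What the plan says.** The Statistical analysis section treats the intervention as a fixed effect, handles correlation due to the subject with random effects, and then spells out the error terms: "The multi-level model will have errors due to within-subject variation and due to between-cluster variation (between subject variance"). It mentions no participant-by-phase or participant-by-treatment term and no robust variance. The remedy for extra variation is: "In the event that the study generates over-dispersed data, we will use a negative binomial regression with the approach as described above". The fallback therefore keeps the same random structure.

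The unit of the regression is not fixed. The Primary outcome section calculates a rate for every dialysis treatment, which suggests session rows. The Sample size calculation works with counts over a whole phase, which suggests phase totals: "two Poisson processes with average rates of IDH equal to 7 (control) and 5 (intervention) episodes over 24 runs".

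That section states that "a sample size of 30 participants would provide a power of 90% to demonstrate a 30% reduction in the rate of IDH", "with a two-sided alpha of 0.05". It calls one episode per run a conservative assumption because "it is likely that more than one episode will occur per run, increasing the study power".

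**The concern.** In a two-period crossover a participant intercept cancels from the treatment comparison. What remains is (a) Poisson sampling noise within each phase and (b) any genuine shift in that participant's rate between the two phases. The stated model carries (a) but names nothing for (b).

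Some shift is plausible. The protocol reassesses dry weight and critical blood volume every week and follows changes in antihypertensive medication as an outcome. Its exploratory subgroup analysis also allows that benefit may differ between participants.

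If (b) is not zero, the primary confidence interval is too narrow, the p-value too small, and the stated power too high. A fallback triggered by over-dispersion helps only if the extra variation is visible at the level at which the rows are defined.

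**Working it through.** **Inputs from the protocol:** N = 30; 7 (control) against 5 (intervention) episodes per 24 runs; two-sided alpha 0.05; each participant in both phases. **Assumed, not in the protocol:** τ, the SD of the participant-by-phase effect on the log-rate scale, from 0 to 0.4.

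**1. The protocol's own figure.** With equal exposure, the random-intercept Poisson estimate is the log ratio of the two totals.
- SE = √(1/(30×7) + 1/(30×5)) = √0.01143 = 0.1069
- Power = Φ(ln(7/5)/0.1069 − 1.96) = Φ(3.148 − 1.96) = 0.88
- At an exact 30% reduction (7 against 4.9), power is 0.91.

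The stated 90% is reproduced, with τ = 0.

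**2. Type I error with τ > 0.** With no treatment effect the Poisson variance is 2/(30×7), and phase variation adds 2τ²/30. True variance over modelled variance is 1 + 7τ², and type I error is 2Φ(−1.96/√ratio).

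If participants also differ in underlying rate (log SD 0.4, assumed), high-rate participants carry more weight. The ratio becomes 1 + 7(e^(τ²) − 1)e^0.16.

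| τ | 1 + 7τ² | Type I | Type I, between-participant SD 0.4 | Type I, simulated |
|---|---|---|---|---|
| 0.1 | 1.07 | 5.8% | 6.0% | 6% |
| 0.2 | 1.28 | 8.3% | 9.0% | 9% |
| 0.3 | 1.63 | 12.5% | 14.1% | 15% |
| 0.4 | 2.12 | 17.8% | 20.8% | 21% |

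Participant-clustered standard errors with a t reference gave 5% to 6.5% in the same simulation (30 participants, 24 runs per phase).

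**3. Does the fallback help?** At τ = 0.3 the variance-to-mean ratio of a phase total is about 1 + 7×0.09 = 1.63. For one session it is about 1 + (7/24)×0.09 = 1.03, which is hardly visible. Type I error in a second simulation (1,000 trials per setting, between-participant SD 0.4):

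| τ | Poisson, random intercept | Negative binomial, session rows | Negative binomial, phase totals |
|---|---|---|---|
| 0 | 4.7% | 4.7% | 3.9% |
| 0.2 | 7.8% | 7.6% | 4.7% |
| 0.3 | 15.8% | 15.0% | 7.7% |
| 0.4 | 23.3% | 22.2% | 6.9% |

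**4. Power with a correct standard error.** Variance = 1/210 + 1/150 + 2τ²/30. At 7 against 5, power is 81%, 72% and about 61–62% at τ = 0.2, 0.3 and 0.4. Reaching 90% would need 40, 49 and 62 participants.

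**5. At most one episode per run.** With no phase variation, the true SE is √(1 − 7/24) = 0.84 of the Poisson SE, and type I error is 2Φ(−1.96/0.84) ≈ 2%. Adding phase variation, the variance ratio is about (1 − 7/24) + (7 − 7/24)τ² = 0.708 + 6.71τ². This reaches 1 at τ ≈ 0.21.

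**6. Repeat episodes and power.** Let q be the chance that a run is affected and X the episodes in an affected run, with X distributed alike in both arms. Over 30×24 = 720 runs per arm, the variance of a log total is (E[X²]/(E[X]²·q) − 1)/720. Since E[X²]/E[X]² is never below 1, repeats cannot raise power in this setting.
- No repeats: (24/7 − 1 + 24/5 − 1)/720 = 0.00865, SE 0.0930, power 95%.
- Geometric repeats, mean 1.5 (E[X²] = 3, ratio 4/3): variance 0.01246, SE 0.1116, power about 85%. The variance-to-mean ratio is 2 − 1.5×7/24 = 1.56, so the uncorrected Poisson type I error is about 12%.

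**The case against.** Several stronger readings are tempting, and the protocol does not support them.

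- **The interval will be too narrow.** This depends on τ, which the protocol never gives. At τ = 0.1 the effect is trivial. Weekly reassessments vary within a phase and partly average out over eight weeks. The prescription is held constant, a run-in standardises it, and entrants must be medically stable. None of this shows τ is zero, but nothing in the protocol points to 0.3 or 0.4 either.
- **Within-participant variation is treated as noise-free.** It is not. Poisson noise is modelled and within-subject variation is named. Only the extra-Poisson part between phases is missing.
- **The fallback cannot repair this.** True for session rows, largely untrue for phase totals. Repeats within a run are session-level over-dispersion, which a session-level negative binomial does handle: 4.0% type I error in simulation with that source alone.
- **90% is a best case.** Not if runs hold at most one episode, the protocol's own simplification. The correct power is then about 95% without phase variation.

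It can also be said that the plural random effects leaves room for another term, and that an article condenses a fuller plan. That carries some weight. But the next sentence enumerates the variance components, so this is a stated specification and not a silence.

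**Conclusion.** The concern holds in conditional form. As written, the primary standard error omits extra-Poisson variation between a participant's phases, and it can be wrong in either direction.

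Under Poisson counts, type I error is about 6%, 9%, 15% and 21% at assumed τ of 0.1, 0.2, 0.3 and 0.4. If runs hold at most one episode, the Poisson standard error is too wide until τ reaches about 0.2 and too narrow beyond that.

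The unit of analysis matters as much as τ: at τ = 0.3 to 0.4 the fallback leaves 15% to 22% with session rows and about 7% to 8% with phase totals. The statement that repeats increase power is not generally true. It would need repeats that behave like independent events, or a treatment that also reduces repeats, and the protocol states neither.

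**What to change.** In the Statistical analysis section, name the unit and the error structure. Either:

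- fit the primary Poisson model to the episode count per participant-phase, with log dialysis hours as offset, participant-clustered standard errors and a t reference on n − 1 degrees of freedom; or
- keep session rows and add a participant-by-phase random effect.

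These are different estimators, so choose one in advance. The first also corrects errors that are too wide when runs hold at most one episode. Drop the data-dependent switch to negative binomial.

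In the Sample size calculation, state that the 90% assumes no participant-by-phase variation, give power over a range of τ, and delete the claim that repeat episodes increase power.

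Cost: wording only, with data already to be collected. The interval will usually be somewhat wider. With no phase variation the loss is small: replacing 1.96 by the t value of 2.045 on 29 degrees of freedom takes power from Φ(3.148 − 1.96) = 88% to Φ(3.148 − 2.045) = 86–87%. The stated power becomes less favourable.

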### Ethics

Ethical approval has been granted from the University of Calgary Research Ethics Board. The research coordinator will determine patient eligibility, obtain consent from participants for participation in the study and access the sealed envelope containing allocation details. The coordinator will obtain the HD run sheets and submit them to an independent data entry clerk who is blinded to allocation. All data are kept strictly confidential. The principal investigator (JM) and study personnel (KL) are responsible for coordination of the study. The trial is registered with Clinicaltrials.gov (NCT01988181).

## Discussion

Randomized studies assessing the role of BVM and BVM-guided UF biofeedback in the prevention of IDH are limited and of low quality. One the largest studies assessing BVM *without* biofeedback, which was done by Reddan *et al.*, randomized 443 participants to BVM or conventional HD over a 6-month period. Participants in the BVM group had UF rates adjusted at the discretion of the bedside dialysis nurse with a suggested UF algorithm. Due to the need for manual adjustment of the UF rate, it is unclear if the nurses promptly responded to changes in relative blood volume using the suggested algorithm. In fact, the participants randomized to BVM had increased hospitalization and mortality, which may have reflected a lack of adherence to the UF algorithm, or alternatively could have been related to more cautious fluid removal due to the feedback provided by the BVM device [33].

However, when BVM is combined with biofeedback there may be a beneficial reduction in IDH and blood pressure [31, 32, 41, 54]. In a 16-week randomized crossover study by Dasselaar *et al.*, 28 hypertensive patients were randomized to either BVM-guided UF and sodium biofeedback or standard HD for blood pressure and volume control. Despite a significant reduction in blood pressure of 22.5/8.3 mm Hg in the BVM group and extracellular water to body volume ratios when compared to the standard HD group, the overall weight did not change. Although the values were not reported, this study also found a statistically significant reduction in dialysis hypotension [54]. A recent meta-analysis of six studies using BVM-guided biofeedback reported a 39% overall reduction in the number of dialysis sessions complicated by IDH [55]. Of the six studies assessing IDH, three did not have IDH as the primary outcome. Five studies employed an intervention that included both dialysate sodium and UF biofeedback [31, 34, 56–58]. The combination of dialysate sodium and UF biofeedback over UF biofeedback alone raises concerns regarding the potential for sodium loading and resultant interdialytic weight gain through increased plasma osmolality and thirst, perpetuating the vicious cycle of IDH. In addition, the duration of the intervention phase in these studies ranged from 2 weeks to 6 months, with the majority using a short 2- to 4-week intervention, putting the long-term sustainability of the intervention into question. Three did not have a washout period between the intervention and control groups, and one did not have a run-in phase. The majority of the studies did not assess for changes in body fluid composition, nor did they address patient quality of life. In addition, the available studies are generally of low quality due to unclear randomization, unclear exclusion criteria and the inclusion of low numbers of IDH-prone participants [55].

Only one randomized crossover study (26 HD participants) examined the impact of BVM-guided UF biofeedback on patient symptoms during dialysis. The primary outcome was the percentage reduction in dialysis symptoms, which was 8%. The secondary outcome was a reduction in hypotension [41]. The trial has several weaknesses including short duration (6 weeks), a lack of a washout period, a nonstandard definition of IDH and potential bias due to its industry-funded nature.

Currently, a prospective multi-center triple-arm parallel-group crossover randomized controlled trial is in progress. It is comparing BVM-guided UF biofeedback and blood thermal monitoring temperature biofeedback, to BVM-guided UF and sodium biofeedback, and to standard HD in fluid overloaded HD patients. The primary outcome in this study is the proportion of HD sessions that were complicated with intra- and post-dialytic symptoms related to UF, irrespective of blood pressure. The secondary outcomes include both symptomatic and asymptomatic IDH, using a non-standard definition of a >40 mm Hg drop in systolic blood pressure [59]. In contrast, our study focuses on enrolling symptomatic IDH patients, a standard IDH definition of ≥20 mm Hg, and studying only BVM-guided UF biofeedback without another accompanying biofeedback technology.

We have described our methods for recruitment, randomization, allocation concealment, dialysis intervention, outcome assessment and data collection methods in detail. The study protocol was developed according to the Standard Protocol Items: Recommendations for Interventional Trials (SPIRIT) 2013 [60]. It will be conducted and the results reported following the Consolidated Standards of Reporting Trials (CONSORT) statement [35].

## Trial status

Enrollment began in June 2014 with an expected completion date of July 2015.

## Abbreviations

BNP: brain natriuretic peptide
BVM: blood volume monitoring
CONSORT: Consolidated Standards of Reporting Trials
DRIP: dry-weight reduction in hypertensive hemodialysis patient
ECFV: extracellular fluid volume
HD: hemodialysis
ICFV: intracellular fluid volume
IDH: intradialytic hypotension
SPIRIT: Standard Protocol Items: Recommendations for Interventional Trials
UF: ultrafiltration.
